## Abstract

**Background:**

It is recommended that children should avoid eating dinner, being physically active, or using screens in the hour before bed to ensure good sleep health. However, the evidence base behind these guidelines is weak and limited to cross-sectional studies using questionnaires.

**Objective:**

The aim of this randomized crossover trial was to use objective measures to experimentally determine whether recommendations to improve sleep by banning electronic media, physical activity, or food intake in the hour before bed, impact sleep quantity and quality in the youth.

**Methods:**

After a baseline week to assess usual behavior, 72 children (10-14.9 years old) will be randomized to four conditions, which are (1) avoid all 3 behaviors, (2) use screens for at least 30 minutes, (3) be physically active for at least 30 minutes, and (4) eat a large meal, during the hour before bed on days 5 to 7 of weeks 2 to 5. Families can choose which days of the week they undertake the intervention, but they must be the same days for each intervention week. Guidance on how to undertake each intervention will be provided. Interventions will only be undertaken during the school term to avoid known changes in sleep during school holidays. Intervention adherence and shuteye latency (time from getting into bed until attempting sleep) will be measured by wearable and stationary PatrolEyes video cameras (StuntCams). Sleep (total sleep time, sleep onset, and wake after sleep onset) will be measured using actigraphy (baseline, days 5 to 7 of each intervention week). Mixed effects regression models with a random effect for participants will be used to estimate mean differences (95% CI) for conditions 2 to 4 compared with condition 1.

**Results:**

Recruitment started in March 2024, and is anticipated to finish in April 2025. Following data analysis, we expect that results will be available later in 2026.

**Conclusions:**

Using objective measures, we will be able to establish if causal relationships exist between prebedtime behaviors and sleep in children. Such information is critical to ensure appropriate and achievable sleep guidelines.

**Trial Registration:**

Australian New Zealand Clinical Trials Registry ACTRN12624000206527; https://tinyurl.com/3kcjmfnj

**International Registered Report Identifier (IRRID):**

DERR1-10.2196/63692

## Introduction

Ensuring children and youth receive sufficient good-quality sleep is paramount for optimal health and well-being [1,2]. However, poor sleep health is a major issue worldwide [3], including in New Zealand [4]. Children with poor sleep are at increased risk of excess weight [5], do not do as well at school [6], are less resilient [7], and have poorer mental health [8]. Thus, advisory groups worldwide [9-11] endorse several “sleep hygiene” behaviors that are thought to promote good sleep health, encompassing sleep habits, environments (eg, bedding and temperature), and prebed behaviors (limiting the use of electronic media, vigorous exercise and active play, or the consumption of food in the hour before bed). However, the evidence base illustrating that these strategies actually influence sleep is variable. Strong support exists for some aspects including consistent bed and wake times, age-appropriate sleep duration, bedtime routines, sleep independency, and no bedroom electronics [12,13]. By contrast, evidence supporting any effect of screen time, physical activity, or food intake in the hour before bed is less definitive [12-15].

While a potential relationship between electronic media and subsequent sleep has received the most attention, the evidence on which these guidelines are based is mainly from cross-sectional studies that cannot determine causality [16,17]. The much smaller evidence base of prospective studies reports inconsistent findings, with most research not showing any significant relationship between screen time and sleep [18,19]. Using stronger temporal analyses that examine the effect of screen time on sleep each night have also reported a limited impact of evening screen use [20,21]. Furthermore, most studies to date have used recalls of screen use, which are prone to bias and are likely unable to measure screen time in the modern world [22,23]. While evidence is emerging that has used objective measures of screen time, this has often been restricted to individual devices (predominantly phones) [24,25]. This precludes the measurement of behaviors including multitasking where more than 1 device is used simultaneously [26,27]. A further limiting aspect is that most studies have examined the impact of whole-day screen time, rather than that more immediate to bedtime, thought to be more detrimental to sleep [16,28]. Although some, but not all, questionnaire-based analyses by Hartley et al [29] and Belmon et al [30] have reported that the use of evening electronic media was associated with poorer sleep, objective measurement of bedtime smartphone usage (tracking app) did not support these findings [24].

A recent review suggested that interventions to reduce screen time can improve sleep. However, there are many issues with this literature. Interventions have often included day screen use [31], or not specified evening screen use only [32], or included changes to other behaviors that might also influence sleep such as diet and exercise [31]. Much of the assessment has also been through questionnaires, which have produced conflicting findings [33,34].

Although daytime physical activity is beneficial for evening sleep in some studies [35-38], how physical activity before bedtime impacts sleep (the actual recommendation) in youth is unclear, with very limited data. Matsuyama et al [39] showed no difference in accelerometer-measured physical activity of any intensity between those who went to bed earlier versus later. However, the period examined (after school until bedtime) was considerably longer than the guidelines (1-2 hours before bed), and sleep duration was not examined. While others have reported that youth with morning chronotypes tend to have higher levels of physical activity and lower levels of sedentary behavior [40], such data do not analyze a direct relationship between evening physical activity and subsequent sleep. Presumably, the recommendation about evening activity was developed based on experimental work in adults. However, examination of that research also suggests that evening exercise of moderate to vigorous intensity either has no detrimental effect, or is even protective, improving a range of sleep health outcomes [41-44]. Comparable findings have also been reported in large observational studies using objective measures of both behaviors [45]. Given the dearth of research on youth, who may respond differently to adults, experimental evidence directly designed to answer whether evening physical activity impedes sleep is required.

The final recommendation refers to avoidance of large amounts of food close to bedtime. However, as with screens and activity, relatively few studies appear to have investigated associations between the timing of the evening meal (hereafter referred to as dinner) and sleep outcomes in youth. Cross-sectional data in children show that later dinner meals are associated with parental-reported later bedtimes [46] and shorter sleep duration [47]. However, objective measures of sleep have produced mixed results, with studies showing associations between later evening mealtimes and shorter total sleep time (TST) [48] or later sleep midpoint [49], or no difference in sleep duration between early and late dinner eaters [50]. To date, no experimental evidence analyzing meal timing and sleep appears to have been conducted in youth, although comparable data show no effects in adults [51].

Thus, it appears that very little experimental evidence has directly examined whether any of these prebedtime behaviors adversely affect sleep; critical data for producing evidence-based sleep hygiene guidelines. This is particularly relevant considering that implementation of such guidelines might be challenging for families. For example, both parents and children may find the current blanket ban on screen time before bed difficult, if not impossible, to implement regularly, despite more than half of all parents viewing excessive screen time as their top health concern [52]. Given almost ubiquitous engagement in evening screen use by adolescents [53] and the potential for further stress and conflict in families from screen time “bans” [54,55], an examination of the practicality of such guidelines seems warranted. Encouraging children not to eat late or be physically active in the evenings might also be challenging, given they do not see these behaviors as important for sleep [56]. Whether parents also find the recommendations to restrict food and vigorous activity before bedtime difficult, appears not to have been examined. It is also important that sleep hygiene recommendations do not harm children. For example, given that inadequate physical activity is a major issue for children worldwide [57], restricting children from being active close to bedtime is a misguided effort to improve sleep, and may have unintended consequences on overall activity. Such analyses do not appear to have been examined.

Therefore, the primary aim is to use objective measures to experimentally determine whether screen time, physical activity, or a meal in the hour before bed affects TST.

The secondary aims are to determine (1) whether screen time, physical activity, or a meal in the hour before bed affects sleep onset, wake after sleep onset (WASO), shuteye latency, sleep onset latency, sleep disturbances, and sleep impairment; (2) whether screen time, physical activity, or a meal in the hour before bed affects health-related quality of life; (3) whether restricting physical activity before bed influences physical activity during the day; and (4) how participants and families found the interventions and how realistic they considered them to be.

## Methods

### Study Design

The helpful activities before it is time to sleep (HABITS) study is a randomized crossover trial to experimentally determine whether banning electronic media, physical activity, or food intake in the hour before bed actually impact children’s sleep quantity and quality. Wearable cameras will be used to obtain objective measures of prebed behaviors and accelerometers for objective measures of sleep. The study will be conducted in participants’ homes and at the University of Otago in Dunedin, New Zealand.

All children will undergo a baseline week to establish usual prebedtime behavior and set bedtimes for the intervention weeks. Each participant will follow 4 experimental prebedtime conditions in a randomized order (Figure 1). The comparison or ideal week will be condition A. In condition B (screens week), participants can use any device and undertake any screen behavior. In condition C (exercise week), suitable options will be suggested for both indoor (eg, wrestling and dancing) and outdoor (tag, sports, and walking) activities. In condition D (food week), participants will be asked to eat a large meal in the hour before bed.

Families will follow each intervention condition on the same consecutive 3 days of each intervention week (days 5-7). In total, 3 days will provide sufficient data to determine how each behavior influences sleep, allows a washout between each condition, and is a pragmatic choice to limit participant or researcher burden. As we are examining the effect of the condition on sleep the same night, this amounts to 3 observations/participant/condition, which should give more reliable estimates than 1 observation or condition. Each family can choose what days of the week are days 5-7 for them, as long as the same days apply across all 5 weeks. All interventions will occur during the school term to limit known changes in sleep caused by holidays [58]. Daylight savings will be avoided and lunar patterns will be recorded to examine the potential for confounding across the different phases.

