### Recruitment and Eligibility

#### Overview

Recruitment will take place through social media and community networks. Interested families will complete an eligibility screening questionnaire online (assessing whether their child has, or previously had, a sleep disorder, any medications that may impact sleep, and ability to undertake physical activity), which they will access through local Facebook (Meta) pages or email from the researchers. Children will be eligible to participate if they are 10-15 years old and live in the Dunedin area. Children will be excluded if they have been diagnosed with a sleep disorder or issue or are on medication that may affect sleep. Children who are not eligible will be sent a standardized text or email by their caregiver. We aim to recruit a sample that is broadly representative of the New Zealand population [61].

Before attending the baseline appointment, potentially eligible participants will be asked to select 3 consecutive nights in the week that would work best for them to complete the intervention (eg, Mondays, Tuesdays, and Wednesdays). These days will be classified as days 5-7 for participant baseline (week 1) and intervention (weeks 2-5) weeks. The researchers will then book their baseline appointment on day 1 of the baseline week.

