### Randomization

#### Overview

Once the baseline appointment is completed, participants will be randomized using the REDCap (Research Electronic Data Capture; Vanderbilt University) randomization module [63] to one of 4 intervention group orders using a computer-generated sequence, stratified by age (from 10 to less than 13 years or from 13 to 15 years), with random block sizes of 4 or 8. The 4 group orders are from a Williams Latin square balanced for first-order carryover effects. Usual bedtimes will be discussed with families, based on camera footage from baseline. While bedtime for each night of intervention (ie, nights 5-7 of each intervention week) can be different, each day of the week must be consistent between all 4 intervention weeks.

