### Outcome Measures

#### Sleep

The primary outcome is TST, with secondary outcomes of sleep onset, WASO, shuteye latency, sleep onset latency, sleep disturbances, and sleep impairment assessed using objective and subjective measures (Figure 2). AX3 accelerometers will be worn on the nondominant wrist, 24 hours a day, for 7 days during the baseline week and 3 days during intervention weeks 2-5. These accelerometers provide accurate measures of our sleep variables in this age group, as determined against the gold standard polysomnography [67]. These devices are smaller than a watch, waterproof, unobtrusive, and do not need to be removed for sport or bathing, ensuring high wear time compliance rates [68]. After initialization of the accelerometer, the data will be downloaded with OmGui software (version 1.0.0.30; Open Movement), saved in raw format as .cwa files, then converted into ActiGraph counts for data processing [69]. Sleep variables are obtained using an automated script developed in MATLAB (MathWorks) that uses a count-scaled algorithm to estimate sleep and wake epochs for each individual for each day [70]. Sleep onset is then determined as the start of the first 15 continuous minutes of sleep preceded by 5 minutes of awake. Sleep offset is determined as the last of 15 continuous minutes of sleep followed by 5 minutes of awake. WASO is determined as the number of minutes from the sum of all movement epochs that occur over 5 continuous minutes of awake between sleep onset to offset. TST is determined as the number of minutes from sleep onset to sleep offset minus WASO. The remaining sleep variables of interest will be measured from the stationary video data. Bedtime is determined as the first time the participant gets into bed and under the covers. Shuteye time is determined as the first time the participant stops interacting with any device or person and appears to close their eyes to try and go to sleep. Shuteye latency is calculated as the difference between bedtime and the first shuteye time. Sleep latency is calculated as the difference between shuteye time from the video camera data until sleep onset time from the accelerometer. Sleep disturbances (difficulties falling and staying asleep) and sleep impairment (daytime alertness and sleepiness) will be measured using 2, 8-item PROMIS (Patient-Reported Outcomes Measurement Information System) questionnaires [71]. The questionnaires were originally designed with a 7-day recall and will be used in this context to assess usual sleep disturbances and impairment during the baseline week on day 8 (therefore covering the previous week). An adapted version assessing the previous night only, will be used to measure sleep disturbances on the previous night and will be administered on the morning of days 6, 7, and 8 of each intervention week, asking about “Last night…” rather than “Over the past 7 days.” An adapted version assessing sleep impairment over the previous 3 days will be administered on the evening of day 8 of each intervention week, with the anchors for these questions changing from “Over the past 7 days” to “Over the past 3 days.”

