### Statistical Analyses

Siblings in the same family may wish to participate, and they would be convenient participants, given their familiarity with the intensive intervention protocols. However, siblings represent family clustering that must be statistically accounted for. We examined the intraclass correlation coefficient (ICC) for families in our recent observational repeated-measures study of screen use and sleep in teens [73], which was low (ICC=0.005). Using this ICC and an average family cluster size of 2, the design effect is 1.005 [74], which has a negligible effect on the required sample size (60*1.005=60.3). Therefore, siblings may be recruited but will be assessed at different times throughout the year, will be individually randomized, and will contribute to no more than half the sample (ie, n=36 participants must not have siblings in the study).

Primary statistical analyses will be undertaken using data from adherent days; secondary analyses will use all data. Mixed effects regression models with a random effect for participants nested within a family cluster will be used to estimate mean differences, 95% CI, and *P* values for conditions 2, 3, and 4 compared with condition 1. Residuals will be plotted and visually assessed for homoskedasticity and normality. Adjustments for within-person confounding (eg, lunar phases) will be undertaken as sensitivity analyses. Results will be reported in line with the CONSORT (Consolidated Standards of Reporting Trials) statement extension to crossover trials. Descriptive analyses will also be undertaken to explore participants’ experiences with the interventions as well as their adherence. Relationships between sleep and quality of life measures will be assessed using repeated measures mixed effects analyses.

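### School and non-school nights can be mixed, the stated TST model has no term for night type, and restricting the primary analysis to adherent days can undo the design's balance

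*Protocol article*

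**What the plan says.** Under Study Design, "Each family can choose what days of the week are days 5-7 for them", provided that those days stay the same in all five weeks. Recruitment and Eligibility asks families for the three consecutive nights that suit them; Monday to Wednesday appears there only as an example. Nothing excludes Friday or Saturday night.

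Study Design also states that "All interventions will occur during the school term to limit known changes in sleep caused by holidays". Under Randomization, bedtimes may differ between nights, but "each day of the week must be consistent between all 4 intervention weeks". No rule covers wake time. Allocation is "stratified by age (from 10 to less than 13 years or from 13 to 15 years), with random block sizes of 4 or 8", with no stratum for type of night.

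Under Sleep, the primary outcome is defined thus: "TST is determined as the number of minutes from sleep onset to sleep offset minus WASO".

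Under Statistical Analyses, "Mixed effects regression models with a random effect for participants nested within a family cluster will be used to estimate mean differences" for each active condition against the comparison condition. The primary analysis uses adherent days; all data are used only in secondary analyses. The one named example of a within-person adjustment is lunar phase, as a sensitivity analysis.

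**The concern.** Two separate things can go wrong.

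The first is imbalance. Using the same weekdays in every week balances night type within each child only while all nights are analysed. Once non-adherent nights are removed, a child may contribute a Friday in one condition and not in another. If TST differs by night type and adherence depends on both condition and night type, part of that difference enters the condition contrast.

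The second is effect modification. If a behaviour delays sleep onset, the lost minutes can be regained by waking later, because TST runs to offset. That is more plausible when there is no school the next morning. The pooled estimate would then average a larger school-night effect with a smaller one, in proportions set by family convenience. The Discussion already expects limited effects and intends the results to inform guidelines, so an attenuated estimate could be taken as confirmation.

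**Working it through.** **Inputs from Sample Size:** difference 15 min, SD 35 min (called within-person), 90% power, alpha .05, 60 participants needed, 72 recruited. Study Design gives three nights per condition.

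**Reproducing the plan's figure.** A two-sided paired t-test with 35 min as the SD of the paired difference needs n = 60 (power 90.4%). Read instead as a single-night within-person SD, 35 min gives:
- one night per condition: SD of the difference 35 × √2 = 49.5, n = 117;
- the mean of three nights per condition: SD of the difference 35 × √(2/3) = 28.6, n = 41, and 97.9% power at n = 60.

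The first reading is used below, with 28.6 as the alternative.

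**Possible mix of nights.** Take Friday and Saturday as the non-school nights (an assumption). The seven windows of three consecutive nights contain:

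| Window | Non-school nights |
|---|---|
| Mon–Wed | 0 |
| Tue–Thu | 0 |
| Wed–Fri | 1 |
| Thu–Sat | 2 |
| Fri–Sun | 2 |
| Sat–Mon | 1 |
| Sun–Tue | 0 |

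If all windows are equally likely (also an assumption), the non-school share is f = 6/21 = 2/7.

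**Dilution.** Let r be the share of lost TST slept back on non-school nights. Pooled effect = 15 × (1 − f × r). Neither f nor r is in the document. At f = 2/7 and n = 60:

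| r | Pooled effect (min) | Power, SD 35 | n for 90%, SD 35 | Power, SD 28.6 |
|---|---|---|---|---|
| 0.25 | 13.9 | 86% | 69 | 96% |
| 0.5 | 12.9 | 80% | 80 | 93% |
| 1 | 10.7 | 65% | 115 | 82% |

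At f = 0 the effect stays at 15 min and power at 90% (98% with SD 28.6).

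**Imbalance from adherent days.** Let D be the amount by which mean TST on a non-school night exceeds that on a school night. Suppose a child on Wed–Fri is adherent on all three nights in condition A but not on the Friday in condition B. The A mean contains D/3 from the Friday and the B mean contains none, so that child's B − A difference shifts by −D/3 with no effect of screens at all. Averaged over children, the bias is D times the between-condition difference in the non-school share of adherent nights. It is zero if nights are lost equally across conditions. The document gives neither quantity, so no size can be stated.

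**Precision of a school-night estimate.** Every window keeps at least one school night. Assuming independent nights, and 35 min as the SD of the three-night difference:
- two school nights: SD 35 × √(3/2) = 42.9, SE up 22%, power for 15 min about 76%;
- one school night: SD 35 × √3 = 60.6, SE up 73%, power about 47%.

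**The case against.** The strongest reply is that the design already handles night type. The same days recur in every week and bedtimes are matched by weekday, so across all nights the comparison is balanced within each child. That is correct. A reader might infer that mixing nights biases the pooled contrast in itself; it does not, and the all-data secondary analysis largely keeps this balance. The reply does not cover the primary analysis, which is conditional on adherence.

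A reader might also see a contradiction in excluding holidays while admitting weekends. The document does not support that. A holiday could fall in some condition weeks and not others, whereas a chosen weekend night recurs in all of them.

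It can further be said that the aim is the effect on TST on any night; if a child sleeps later and TST is unchanged, a null for that night is right. This stands, and is why the pooled contrast should stay primary. Sleep onset, shuteye latency and sleep onset latency are secondary outcomes that do not depend on wake time, so an onset delay would still be seen. They would not show whether TST was lost on school nights. Loss through WASO lies outside this mechanism.

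Finally, subgroup analyses are often left to an SAP, and the list of within-person adjustments is open. That lowers the weight of the point. But the article does fix adherent days as the primary set and describes a model without night type, and that combination is what needs attention.

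**Conclusion.** The point holds in a limited form. Free choice of nights, uncontrolled wake time, a TST that includes sleep offset, and a stated model without night type are all in the text. Restriction to adherent days can unbalance night type between conditions, by an amount that cannot be derived from the document.

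Dilution is conditional. It requires freer waking before non-school days, which is reasonable but not stated, and families who choose such nights. At an equal spread of windows the loss runs from slight (86% power) to material (65%), and is milder if the SD of the difference is 28.6. It is nil if all families choose school nights.

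A reader might infer far worse: a 10-minute effect with 59% power, or 5 minutes with 19%. With full recovery of lost sleep, those figures require every family to have one, or two, non-school nights out of three. Nothing in the document supports such extremes as the expected case.

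**What to change.** In Statistical Analyses:

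1. Add to the mixed model an indicator for whether the next morning is a school day. It follows from each family's chosen days. It removes additive night-type imbalance among adherent days and may improve precision.
2. Keep the pooled contrasts of B, C and D with A as primary.
3. Prespecify the condition-by-school-night interaction, with the school-night contrasts of B, C and D against A, as a secondary, supportive analysis. The indicator alone does not address effect modification.

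No new data are needed. The cost is one main-effect term, three interaction coefficients and three further contrasts to report. The school-night estimates will have wider intervals where families chose non-school nights. Given the 76% and 47% power shown above, the plan should say that a null school-night result is not to be read as no effect.
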